### Economic evaluation

Cost-effectiveness will be evaluated from the societal perspective including both direct and indirect costs. Both costs groups will be estimated according to the Dutch guidelines for cost analysis in health care research [38,39] or with the use of the tariffs of the Dutch Central Organization for Health Care Charges [40]. These costs will be measured 4 times during the one-year follow-up. Indirect costs of loss of production due to LBP are not related to health care, but are costs in paid and unpaid labour as a consequence of sickness, sick leave, disability and/or death of a productive person. Mailing the patient monthly a calendar as well as collecting the sick leave data collected in occupational health services database will measure the number of days on sick leave due to LBP. Quality of life will be measured according to the standard Dutch version of the EuroQol [30]. Costs will be summated for each individual patient. Bootstrapping will be used for pair-wise comparison of the mean groups to calculate mean differences in direct, indirect and total costs between the two groups of patients. Confidence intervals (95%) will be obtained by bias corrected and accelerated bootstrapping. A cost-effectiveness ratio will be calculated by dividing the difference between the mean costs of the intervention groups by the difference in RTW between the intervention groups. A cost-utility analysis will also be conducted in which the incremental costs per QALY will be estimated. Reliability of the cost-effectiveness ratios will be graphically presented on a cost-effectiveness plane and acceptability curves.

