### Sample size

We assume that a Hazard Ratio (HR) of 2.0 indicates a relevant difference between the multidisciplinary outpatient care group and the UC group. This HR is based on HRs found in comparable studies in primary care [15,19,34]. Another assumption is that 40 percent of the sick listed patients due to chronic low back pain does not return to work during the follow-up period (12 months after randomization). We expect a dropout rate of 10%, based on experiences with comparable research [35,36]. To get a complete data set of 115 patients, 130 patients with chronic LBP who are sick listed will be included (HR = 2, with a power (1-β) of 80% and a significance level of 5%) [37]. Before starting the inclusion of patients, a two-week visitors' waiting room survey has been done at the departments of orthopaedics and neurology at the VU Medical Center Amsterdam. This survey showed that at these two departments the percentage of patients sick listed because of LBP is low (3–4%). Because of this low percentage, four other hospitals are recruited so the recruitment period of 24 months duration is likely acceptable.

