### Data analysis

All analyses will be performed at patient level. To examine the success of randomization, descriptive statistics will be used to compare the baseline measurements of the two groups. If necessary, analyses will be adjusted for prognostic dissimilarities. The primary independent variable in the analyses will be the treatment (MOC or UC) to which the patient is allocated. The primary dependent variable is sick leave duration in days until full return to own or equal work. Kaplan Meier analyses (including log rank test) will be used to describe the univariate association between group allocation and the sick leave duration until full RTW. The Cox Proportional hazard model will be used to analyze the HR of the RTW rates in both groups in a multivariate model. Longitudinal random coefficient analyses will be used to assess differences between treatment groups in improvement in all secondary outcome measures. The baseline value of the particular outcome variable will be added to the model in order to correct for possible regression to the mean.

All statistical analyses will be performed according to the intention-to-treat principle, i.e. the patients will remain in the group to which they were randomly allocated at baseline. In order to assess whether protocol deviations have caused bias, the results of the intention-to-treat analyses will be compared to per-protocol analyses. Only those patients who complied fully with the intervention protocol will be included.

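### The economic section specifies no baseline adjustment for the QALY difference, although baseline EuroQol is collected; following the text most naturally gives up precision at no saving

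*Protocol article*

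**What the plan says.** Under Economic evaluation, the Protocol article announces the cost-utility analysis in one sentence: "A cost-utility analysis will also be conducted in which the incremental costs per QALY will be estimated". The comparison method named in that section is "Bootstrapping will be used for pair-wise comparison of the mean groups to calculate mean differences"; the sentence goes on to name direct, indirect and total costs as the quantities compared. A ratio of differences is spelled out for return to work. The cost-effectiveness plane and acceptability curves follow. The section gives no QALY formula, no method for comparing QALYs between groups and no covariate step.

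Under Data analysis, secondary outcomes are analysed with longitudinal random coefficient models, and "The baseline value of the particular outcome variable will be added to the model". EuroQol quality of life is one of those outcomes. The same section also has a general rule: the groups are compared at baseline, and analyses are adjusted for prognostic differences where that proves necessary. It names no variables and no criterion.

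Table 3 schedules EuroQol at baseline and at 3, 6 and 12 months. Randomisation is stratified by sick-leave duration and by type of job demands, not by utility.

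**The concern.** The same instrument in the same patients is handled in two ways. As a secondary outcome, EuroQol is analysed with its baseline value in the model. As the source of the QALY, it enters a section whose only stated between-group tool is a bootstrap of group means.

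The longitudinal-model sentence does not naturally reach the QALY, which is one number per patient and is not listed among the secondary outcomes. The general rule might reach it, but only after the baseline data have been inspected. An analyst following the text would therefore most naturally produce an unadjusted QALY difference, or would decide on adjustment after seeing the imbalance.

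Cost-effectiveness is half of the first research question. The QALY difference is the denominator of the cost per QALY and one axis of the plane, and it feeds the acceptability curve. With fewer than 60 patients per arm, avoidable noise in it matters.

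**Working it through.** **The plan's own figure.** No figure is given for QALYs; the only planned number is the sample size for return to work. The inputs are a hazard ratio of 2.0, 80% power, 5% significance (taken as two-sided) and 60% events, since "40 percent of the sick listed patients due to chronic low back pain does not return to work during the follow-up period".
- Freedman: (1.96 + 0.84)² × ((2 + 1)/(2 − 1))² = 7.85 × 9 = 70.6 events; 70.6/0.6 = 117.7, i.e. 118 patients.
- Schoenfeld: 4 × 7.85/(ln 2)² = 65.3, i.e. 66 events; 66/0.6 = 110 patients.
- The stated 115 lies between the two. Dropout of 10% gives 115/0.9 = 128, against 130 stated.

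The sample size is reproduced closely enough and is not in question. It supplies the group size used below: 115/2 = 57.5 per arm.

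**Assumptions not in the documents.** The QALY is a trapezoid area under the curve. Utility SD is 0.25, the correlation of baseline with each follow-up (ρ) is 0.4 (range 0.3 to 0.5), and correlations between follow-ups are 0.6.

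**Weights.** For visits at 0, 0.25, 0.5 and 1 year:
- baseline: 0.25/2 = 0.125
- 3 months: (0.25 + 0.25)/2 = 0.25
- 6 months: (0.25 + 0.5)/2 = 0.375
- 12 months: 0.5/2 = 0.25

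**Carry-over of a baseline difference.** The slope of QALY on baseline is 0.125 + 0.875ρ: 0.39, 0.475 and 0.56 for ρ = 0.3, 0.4 and 0.5, and 0.74 for ρ = 0.7.

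**Size of a chance imbalance.** One standard error of the baseline difference is 0.25 × √(2/57.5) = 0.25 × 0.1865 = 0.047. It shifts the expected unadjusted QALY difference by 0.475 × 0.047 = 0.022 (0.018 to 0.026 for ρ = 0.3 to 0.5).

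**Unadjusted standard error.** In units of SD², the variance of the QALY is the sum of:
- baseline: 0.125² = 0.0156
- baseline with follow-up: 2 × 0.125 × 0.875 × 0.4 = 0.0875
- follow-up variances: 0.25² + 0.375² + 0.25² = 0.2656
- follow-up covariances: (0.875² − 0.2656) × 0.6 = 0.3000

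The total is 0.6688, so SE = 0.25 × √0.6688 × 0.1865 = 0.038.

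**Gain from adjustment.** R² = 0.475²/0.6688 = 0.34. The SE is multiplied by √(1 − 0.34) = 0.81, a cut of about 19%. For ρ = 0.3 and 0.5, R² is 0.23 and 0.46, and the cuts are 12% and 26%.

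**Sensitivity.** Take one common correlation among all visits, from 0.3 to 0.7, and SD from 0.20 to 0.30. The unadjusted SE is then 0.026 to 0.050 and the adjusted SE 0.018 to 0.033, a cut of about 16% (correlation 0.3) to 45% (correlation 0.7). A baseline difference of 0.05 adds 0.05 × 0.125 = 0.006 QALY directly and 0.019 to 0.037 in total.

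**The case against.** A reader might infer that the protocol commits to comparing QALYs as raw group means, so that baseline imbalance passes straight into the cost-utility result. The documents do not support that reading:
- The bootstrap sentence concerns costs. No QALY formula or QALY comparison method is stated, so it is also not stated that the baseline value enters the QALY.
- The general adjustment sentence under Data analysis is not limited to particular outcomes. The economic section neither repeats nor excludes it.
- Carry-over is below 1, and the direct weight of baseline is only one eighth.
- Under randomisation, chance imbalance does not bias the unadjusted comparison systematically. It is part of the sampling variance that the bootstrap already displays. The 0.022 shift, 58% of the SE, is simply √0.34; it is not further error on top of that SE.
- A condensed article may leave QALY construction to the full protocol or analysis plan, so silence on the formula is no fault.

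All of this stands. It limits the point but does not remove it. What the article does set out is a covariate-free comparison in the economic section, baseline adjustment for the same instrument elsewhere, and a general rule triggered by observed imbalance. That rule does not commit to baseline utility. It also misses the main benefit, because adjustment improves precision even when no imbalance is visible.

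**Conclusion.** The point holds as a gap in what is prespecified, with a precision cost. Read naturally, the text leads to an unadjusted QALY difference, or to an adjustment decided after inspecting baseline data. If QALYs are areas under the curve, that difference carries over roughly 0.4 to 0.7 of any chance baseline utility difference (correlations 0.3 to 0.7). Its SE could be about 12 to 26% smaller with adjustment (baseline correlations 0.3 to 0.5, follow-up correlations 0.6). The SD, the correlations and the QALY formula are assumptions; the visit times and group size come from the article. The consequence is lost precision and bias conditional on the observed imbalance, confined to the cost-utility results. Neither the primary return-to-work analysis nor the sample size is affected. It is a worthwhile, nearly free improvement rather than an error that invalidates an analysis.

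**What to change.** State in advance, under Economic evaluation or in the analysis plan, how the QALY is computed from the four EuroQol assessments. State also that the QALY difference is estimated by regression on arm and baseline EuroQol utility within each bootstrap sample, regardless of the imbalance observed. Pair that adjusted difference with the cost difference from the same bootstrap sample, and use these pairs for the cost per QALY, the plane and the acceptability curve. Adding the four randomisation strata to the regression and resampling within arm are optional.

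The cost is one regression step in the bootstrap code. Baseline EuroQol is already in the schedule, so no extra data, visits or patients are needed.

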## Discussion

This study addresses an important question because LBP is a major health and economic problem. In the BRIDGE-study we focus on patients, sick listed because of chronic LBP, who are seeking for outpatient care by consulting a medical specialist. These patients frequently have problems with their working capacity [8]. However, there is strong evidence that most clinical interventions for chronic LBP are not effective for RTW. Therefore, a protocol is developed to evaluate the clinical and cost effectiveness of a multidisciplinary outpatient care program situated in both primary and outpatient care for patients with chronic LBP attending a medical specialist. The multidisciplinary outpatient care program consists of a case management protocol including a workplace intervention protocol and a GA program. Recent research shows that long-term work disability is not only due to patient's personal characteristics but is also a consequence of an interaction with the patient's environment (the workplace system, compensation system, healthcare system) [41]. In this study the GA is directed to the patient's personal characteristics, and illness behavior (cognitions, coping) via operant conditioning, the workplace intervention will focus on the work system (worker, supervisor) while the coordination of care of the care manager will be directed to focus on the health care system to a common RTW-goal.

### Strengths and limitations of this study

The main focus of this study is RTW which we will measure both monthly by calendar for one year as well as check against data records of the occupational health services after the follow-up period ends. This will avoid information bias for our primary outcome.

Another strength of this study is that, besides a quantitative analysis, a qualitative analysis will be done as well. Data for the qualitative analysis are gathered by focus groups and an in-depth interview. We have chosen for organizing focus groups because it has several advantages. First, it provides insight in the sources of complex behaviour and motivations. It also gives better insight on consensus and disagreement between the participants around topics. The added value of an in-depth interview is that the patients can tell about their experiences with the multidisciplinary outpatient care program in a more comprehensive way then they can do in the questionnaires. Moreover the patients can discuss topics in the depth interview, which the questionnaire will not been offer them. With all these data it is possible to identify aspects of the working mechanism (black box) behind the multidisciplinary outpatient care program. It will be possible to clarify the elements that contribute to the effects of the multidisciplinary outpatient care program, which results in more valid conclusions.

There are also some limitations. First, blinding is a validity criterion in most reviews, which is not possible in this trial. It is impossible to blind patients and healthcare providers due to the character of the workplace intervention and the GA program. Another possible source of bias is the difference in attention patients might receive, the so-called 'Hawthorne effect'. Patient in the multidisciplinary outpatient care group will receive more attention than the patient in the UC group. This might lead to overestimation of the effect of the multidisciplinary outpatient care program.

Our economic evaluation will be performed from the societal perspective. It would be desirable to do additional analysis from the employer's perspective, since interventions in occupational care in the Netherlands have to be paid by employers. However, the population of this study is working for different companies, which are connected to different occupational health care providers or is self-employed. Thus, gathering all the information needed for the economic evaluation is impossible.

### Impact on this study

It has been shown in a primary care setting that occupational interventions resulted in a reduction in sick leave of 29–105 days, depending on the occupational intervention applied and the population [15,42]. This equals an average reduction of sick leave duration of 33%. If a comparable reduction of sick leave duration of patients with chronic LBP of who attend outpatient clinics can be achieved, such cost reductions will be obviously substantial for the Netherlands. Therefore, to improve RTW of patients with chronic LBP in outpatient care and to reduce costs, multidisciplinary outpatient care can have a considerable impact.

## Abbreviations

GA, graded activity; GP, general practitioner; HR, hazard ratio; LBP, low back pain; MOC, multidisciplinary outpatient care; OP, occupational physician; Par-Q, Physical Activities Readiness Questionnaire; PCI, Pain Coping Inventory scale; RCQ-24, Roland – Morris Disability-24 Questionnaire; RCT, randomized controlled trial; RTW, return to work; UC, usual clinical medical care; VAS, Visual Analogue Scale.
